**Missing data**

Missing data will be handled by group mean imputation.

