## **Sample size**

The sample size calculation is based on a standardised effect size of 0.49, corresponding to a group difference in primary outcome VAS pain of 12 points on a scale of 0-100 (corresponding to a mean difference of 1,2 points on a 1-10 NRS scale). This difference was found in a recent systematic review of 44 high-quality exercise trials for knee OA pain (3537 participants) (56). With this estimated effect, 60 participants in each group is required to achieve 75% power to reject the null hypothesis, with alpha level set to 0.05.

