## **Timing of outcome assessments**

All outcome variables were collected at baseline, and at follow-up (6 weeks post baseline) in both arms. However, trial was stopped on 19th March 2020 due to the COVID-19 pandemic resulting in having only 105 eligible participants completing both visits.

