## **Section 4: Statistical Principles**

### **Confidence intervals and p-values**

Alpha level will be set to 0.05. 95% confidence intervals will be presented (if data allows for parametric analyses).

Adjustments for multiplicity will not be performed. However, primary outcome is defined and will be the main focus for the results interpretation. Remaining analyses will be considered exploratory, and interpreted in light of the general pattern of effects rather than solely based on individual p-values.

Adherence to the i-BEAT OA will be defined as percentage patient completed activities of those distributed by the platform per week. Number of non-compliant participants will be reported.

Analyses will be based on the Intention to treat (ITT) population. Since there are no risks associated with i-BEAT OA, safety analyses will not be performed.

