### **Analysis methods**

The distribution for each difference score will be evaluated. If the score follows an approximately normal distribution with no apparent outliers, between group differences will be analysed through ANOVA with adjustment for baseline scores (ANCOVA). Due to the randomisation, no systematic differences between groups are expected and hence no control for further “confounding” will be performed. Results for the between group comparison will be presented as “difference in mean difference” with accompanying 95% confidence intervals.

Within group differences from baseline to follow up will be evaluated through pre-post mean difference with accompanying 95% CI. Differences/changes with confidence intervals not covering “0” will be considered statistically significant. Standardised effect sizes (Cohen’s D) will be computed (mean difference/baseline SD).

If the difference scores clearly deviate from a normal/symmetric distribution, the comparisons will instead be performed through non-parametric analyses. For the

between group comparisons, Mann-Whitney test will be applied and for the within group comparison, Wilcoxon signed rank test will be used. Results will be presented as median scores (IQR) and p-values. No adjustment for baseline scores will be performed, as the non-parametric tests do not allow for this.

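### Filling missing outcomes with the group mean understates the standard error, so the primary test runs above 5% by an amount that depends on how many randomised participants lack follow-up

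*Combined protocol and SAP*

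**What the plan says.** SAP Section 6, Missing data, consists of one sentence: "Missing data will be handled by group mean imputation". It does not say whether the change score or the week-6 score is filled. Neither the SAP nor the protocol mentions a variance correction, multiple imputation, a complete-case analysis or a sensitivity analysis.

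The rule meets these other parts of the plan:

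- **Population.** SAP Section 4: "Analyses will be based on the Intention to treat (ITT) population". The set is not defined further.
- **Error rate.** SAP Section 4: "Alpha level will be set to 0.05", with 95% intervals when the analysis is parametric.
- **Model.** SAP Section 6, Outcome variables and Analysis methods: the outcome is the baseline-to-week-6 difference, compared between arms by ANCOVA adjusted for baseline.
- **Fallback.** If the differences are clearly non-normal: "Mann-Whitney test will be applied and for the within group comparison, Wilcoxon signed rank test will be used". Medians, IQRs and p-values are reported, without baseline adjustment.
- **Amount of data.** The protocol plans 67 per arm (134 in total) and expects 10-12% dropout (Synopsis) or 12% (Sample size and justification). SAP Section 3, Timing of outcome assessments, reports that the trial stopped on 19 March 2020, "resulting in having only 105 eligible participants completing both visits". The number randomised is not given.

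**The concern.** A value filled with the arm mean has no spread of its own, yet the software counts it as an observed participant. The estimated difference hardly moves, but its standard error falls for two reasons: the SD is smaller and n is larger. The error is anti-conservative, so the more data are missing, the easier it is to declare a difference.

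The type I error and interval coverage of the NRS comparison are at stake, and Section 4 makes that outcome the main basis for interpretation. The same rule would narrow the within-group intervals, which Section 6 calls significant whenever they exclude zero, and would carry over to the secondary outcomes.

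**Working it through.** **Reproducing the plan's own figure.** The SAP sample size is "based on a standardised effect size of 0.49", alpha 0.05, 75% power, 60 per group. Taken as two-sided (inferred from the 95% interval), the formula gives 58 per group by the normal approximation and 59 by the t-test. Power at 60 is 76.5% or 75.9%. Inflating for dropout, 60/0.90 gives 67 and 60/0.88 gives 69, against 67 planned. The stated size reproduces within rounding, so alpha 0.05 two-sided is the right benchmark.

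**Effect of the fill.** Let n be randomised per arm, m the missing fraction and s the SD of observed outcomes, with data missing completely at random.

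- Variance after filling: the same sum of squares spread over n values, about s²(1 - m).
- Reported SE: √(2s²(1 - m)/n).
- True SE: √(2s²/(n(1 - m))).
- Ratio of reported to true: 1 - m.
- Real two-sided alpha: 2(1 - Φ(1.96(1 - m))).

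The third column below shows how many would have been randomised for 105 completers to correspond to each m, that is 105/(1 - m).

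| m | Reported / correct width | Randomised if 105 completed | Real alpha |
|---|---|---|---|
| 0 | 1.00 | 105 | 5.0% |
| 5% | 0.95 | about 111 | 6.3% |
| 10% | 0.90 | about 117 | 7.8% |
| 12% | 0.88 | about 119 | 8.5% |
| 15% | 0.85 | about 124 | 9.6% |
| 20% | 0.80 | about 131 | 11.7% |
| 29/134 = 21.6% | 0.78 | 134 | 12.5% |

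**Simulation of the planned ANCOVA.** 67 per arm, 20,000 null trials per setting, assumed baseline to follow-up correlations of 0.3, 0.5 and 0.7, filling either the change or the follow-up score:

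| Missing per arm | ANCOVA after filling | ANCOVA, observed cases |
|---|---|---|
| 3 of 67 (4.5%) | 5.8-6.4% | 4.7-5.2% |
| 8 of 67 (11.9%) | 8.4-8.7% | 4.8-5.2% |
| 14 of 67 (20.9%) | 12.0-12.4% | 4.9-5.2% |

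A smaller simulation on integer scores 0-10 (4,000 null trials, correlation 0.5) gave 8.0-8.5% at 12% missing, 11.6-13.0% at 21.6%, and 5.0% for observed cases.

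The simulated reported SE, divided by the observed-case SE, was 0.88-0.93 with 8 missing and 0.80-0.87 with 14. This can sit above 1 - m because filling also makes the estimate noisier than the observed-case estimate. The rejection rates nonetheless follow the formula.

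**Mann-Whitney branch** (4,000 null trials per setting). Filling change scores creates a block of ties in each arm: 11-12% rejection with 8 of 67 missing and 21-23% with 14. Filling follow-up scores gives about 6% and 8%.

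**The case against.** **The size is not known.** A reader might infer that the test in this trial actually runs at 8% to 13%. The documents do not support that. The 10-12% dropout is a planning figure. The 21.6% assumes that all 134 were randomised, but the trial stopped early and some or most of the missing 29 may never have been enrolled. With 2 of 55 missing per arm a simulation gave about 5.8%, and with none missing the rate is exactly 5%. This objection stands: every rate must be conditional on m. It does not remove the defect, because the rule inflates the error for any m above zero.

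**Group might not mean arm.** If the mean were pooled over both arms, simulation keeps type I error at about 5% (4.97% and 5.12%) and the harm becomes a diluted effect. Since the SAP uses group for trial arm in its between-group and within-group comparisons, arm is the natural reading.

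**Own baseline.** A reader might also infer that the method always ignores the participant's own baseline. That holds only if the week-6 score is filled. If the change is filled, the implied week-6 score is the person's own baseline plus the arm's mean change. The SAP does not say which.

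**Scope.** The interval claim concerns the ANCOVA branch only, as the fallback reports no interval. The remaining outcomes are labelled exploratory, so an elaborate procedure for each is not required. An imputation model using stratification factors cannot be specified from these documents, since randomisation is called stratified but no factor is named.

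**Conclusion.** The rule is wrong as written and should be changed before the primary analysis is relied on. On the ANCOVA branch the reported interval is about (1 - m) of its correct width. The nominal 5% test runs at about 6% with 5% missing, about 8-9% at the protocol's 10-12% dropout, and about 12-13% only if all 134 were randomised and 105 completed. On the Mann-Whitney branch, for about 12-21% missing, the rate is about 6-8% if follow-up is filled and 11-23% if change is filled.

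These figures assume that group means arm, that missingness is completely random and equal between arms, and that the test is two-sided. If dropout depends on outcome, bias is added, because those lost are given the average of those who stayed. The mechanism is certain; its size here waits on the number randomised.

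**What to change.** Delete group mean imputation. For the primary NRS comparison, specify one method that does not treat filled values as observed:

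- baseline-adjusted ANCOVA on observed cases, or an equivalent likelihood-based repeated-measures model; or
- multiple imputation by arm, using baseline NRS and other collected baseline variables, combined with Rubin's rules.

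With a single follow-up visit the first option is enough to restore the nominal 5% under completely random missingness. Add one sensitivity analysis for outcome-related missingness, for example a delta adjustment that makes missing outcomes worse than observed ones. State the numbers randomised and missing in each arm, and do not mean-impute the secondary outcomes.

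The cost is a change of SAP wording and a little programming. No new data are needed. The interval will be wider, which is its correct size.

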**Harm**

No risks are associated with the intervention; however we will record any serious adverse event or harms and will report in publications.

**Statistical software**

The data will be analysed using StatsDirect V3.2.10, SigmaXL 8.15 and SPSS v24
